### Intervention programs

Treatment will commence within one week of the baseline assessment. Each session in the intervention programs will last approximately 30-60 min depending on group allocation. The participants in each treatment group will be asked to practice their prescribed exercises once daily for 6 weeks and complete an exercise diary to monitor compliance and record adverse events. The physiotherapist will provide the elements of treatment and a home exercise program based on the initial and progressive assessment of participant’s cervical joint, muscular, and sensorimotor and balance dysfunctions (as relevant to group allocation). Description of the intervention programs are summarized in Tables 2 and 3. Exercise prescription and progression are presented in Table 4. The physiotherapist will progress the participants exercise programs to the next level once they have achieved the target of the current level.

**Table 2 Tab2:** Description of the intervention programs

Intervention	Description	Time (minutes)
Local neck treatment	Cervical mobilization	10
	Specific therapeutic exercises	20
Local treatment plus sensorimotor control exercises	Cervical mobilization	10
	Specific therapeutic exercises	20
	Sensorimotor exercises	15
Local treatment plus balance exercises	Cervical mobilization	10
	Specific therapeutic exercises	20
	Balance exercises	15
Local neck treatment plus sensorimotor control and balance exercises	Cervical mobilization	10
	Specific therapeutic exercises	20
	Sensorimotor exercises	15
	Balance exercises	15

**Table 3 Tab3:** Description of modalities used in the intervention programs

Modality	Description
Cervical mobilization [57]	Low-velocity passive mobilization techniques to the symptomatic cervical segments as determined by the physiotherapist’s clinical examination. Physiotherapists are free to select from what are termed passive accessory and physiological movement techniques as deemed relevant to the individual participant based on the initial and progressive reassessments.
Specific therapeutic exercises [26, 58, 59]	Cervical flexors
	(i) Train craniocervical flexor (CCF) activation and holding capacity. Participants learn the correct movement and train to hold the contraction with and without feedback in progressively more difficult inner range positions.
	(ii) Train the interaction of deep and superficial cervical flexors in movement patterning and functional tasks.
	(iii) Train co-contraction of the deep cervical flexors and extensors.
	(iv) Train strength and endurance of the cervical flexors.
	Cervical extensors
	(i) Train craniocervical extensors and rotators (head extension, head rotation < 40°) with the cervical spine in a neutral position.
	(ii) Train cervical extension to bias the cervical extensors (extend cervical spine keeping the craniocervical region in a neutral position)
	(iii) Train strength and endurance.
	Axioscapular muscles
	(i) Train scapular muscles in particular the upper/ middle/ lower trapezius and serratus anterior in both open and closed chain positions, with and without load and movement of the upper limb.
	(ii) Train correct scapular posture.
	Postural correction exercise
	(i) Train a neutral spinal posture from first treatment.
	(ii) Train scapulothoracic and cervical postures. Participants train to actively correct their posture and maintain for 10s. Practice is in sitting, standing (2-3 times an hour).
Sensorimotor exercises [7, 59]	Cervical JPS. The participants practice moving their head to points in different directions initially with eyes open, using a laser pointer mounted onto a lightweight headband. This practice will involve relocating the head back to a neutral posture or to predetermined points in range. The exercise is progressed by closing the eyes and by changing directions and ranges of movement.
	Cervical movement sense. The participants practice tracing horizontal and vertical lines on a chart on the wall focusing on accuracy and secondarily speed using a laser pointer mounted onto a lightweight headband for feedback on performance. Exercises are progressed by increasing speed and tracing more intricate patterns such as a figure of eight, zig-zag or an alphabet pattern.
	Oculomotor control exercises
	(i) Train eye follow. The participants follow a target moving from side to side and up and down while keeping their head still.
	(ii) Train gaze stability exercises. The participants perform active movements, while fixing their gaze on the target. Progressions include increasing the target’s speed, changing the participant’s position and changing visual background and focus point.
	(iii) Train eye head co-ordination exercises. The participants move their eyes and head in the same direction to focus on a target. Progressions include moving the eyes first then the head and moving eyes and head in opposite directions.
Balance exercises [7, 59]	The training starts with static balance and progresses to dynamic balance and challenging gait. The exercises will be progressed by closing the eyes, altering the support surface (i.e. a soft surface), concurrent voluntary movements, or increasing speed.

**Table 4 Tab4:** Details of the exercise progression

Exercise	Level	Details	Targeted repetitions
Cervical flexors	1	Re-education of CCF movement pattern	
		Supine, knees bent	
		- Gentle and controlled nodding action facilitated with eye movement	10 reps
		Holding capacity	
		Supine, knees bent	
		- Repeated and sustained CCF progressing from 22 to 30 mmHg	10 s holds × 10 reps
	2	Interaction between the deep/superficial cervical flexors	
		Sitting	
		- Controlled head movement through range of extension and return to neutral	10 reps
		Co-contraction of the deep cervical flexors/extensors	
		Sitting	
		- Isometric cervical rotation facilitated with eye movement (left/right sides)	5 s holds × 5 reps
	3	Strength/endurance of the cervical flexors	
		Sitting	
		- Isometric CCF in a range of cervical extension	10 s holds × 10 reps
		- Lifting the head off the wall (with the chair up to 30 cm away from the wall)	10 s holds × 10 reps
		Supine	
		- Lifting the head off a pillow (2, 1 then 0 pillows as per participant’s capacity)	10 s holds × 10 reps
Cervical extensors	1	Re-education of extension movement pattern	
		Prone on elbows/four-point kneeling positions	
		- Craniocervical extension	3 sets of 5 reps
		- Craniocervical rotation (< 40°)	3 sets of 5 reps
		- Cervical extension while keeping the craniocervical region in a neutral position	3 sets of 5 reps
	2	Co-contraction of the deep cervical flexors/extensors	
		Sitting	
		- Isometric cervical rotation facilitated with eye movement (left/right sides)	5 s holds × 5reps
	3	Strength/endurance of the cervical extensors	
		Prone on elbows/four-point kneeling positions	
		- Isometric hold in range of cervical extension	10 s holds × 10 reps
		- Addition of progressive load (light weights attached to head) as per patient’s capacity	
Axioacapular control	1	Re-education of scapular movement control	
		Side lying with arm elevated 140°/sitting	
		- Passive repositioning of the scapular	10 reps
		- Active repositioning of the scapular	10 reps
		Holding capacity	
		Side lying with arm elevated 140°/sitting	
		- Active repositioning the scapular posture and isometric hold	10 s holds × 10 reps
	2	Axioscapular muscle control	
		Sitting	
		- Arm movement without load (external rotation/abduction/flexion < 30°)	10 reps
		- Arm movement without load throughout range	10 reps
		Prone on elbows/four-point kneeling position	
		- Thoracic lift (serratus anterior) and isometric hold	5 s holds × 5 reps
	3	Strength/endurance of axioscapular muscles	
		Sitting	
		- Arm movement with load (external rotation/abduction/flexion < 30°)	10 reps
		- Arm movement with load throughout the range	10 reps
		Prone	
		- Lift the shoulder off the bed and hold without arm load	10 s holds × 10 reps
		- Lift the shoulder off the bed and hold with arm load	10 s holds × 10 reps
Postural correction	1	Correction of spinal posture	
		Sitting	
		- Active upright sitting initiated with lumbo-pelvic movement	10 s holds × 10 reps
	2	Correction of spinal posture and scapular orientation	
		Sitting	
		- Actively positioning the scapular in a neutral posture while maintaining spinal posture	10 s holds × 10 reps
	3	Spinal and scapular correction plus occipital lift	
		Sitting	
		- Actively lengthen the back of the neck while maintaining spinal and scapular posture	10 s holds × 10 reps
Cervical joint position sense	1	Relocation with laser feedback	
		Sitting	
		- Head relocating to neutral position with eyes opened (vertical/horizontal)	5 reps × 3 sets
		- Head relocating to predetermined position in range with eyes opened (vertical/horizontal)	5 reps × 3 sets
	2	Relocation with laser feedback	
		Sitting	
		- Head relocating to neutral position with eyes opened (diagonal)	5 reps × 3 sets
		- Head relocating to predetermined position in range with eyes opened (diagonal)	5 reps × 3 sets
		- Head relocating to specific targets with eyes opened (all directions)	5 reps × 3 sets
	3	Relocation with laser feedback	
		Sitting	
		- Head relocating to neutral position with eyes closed (all directions)	5 reps × 3 sets
		- Head relocating to predetermined position in range with eyes closed (all directions)	5 reps × 3 sets
Cervical movement sense	1	Movement sense training with laser feedback	
		Sitting	
		- Tracing a line (vertical/horizontal)	5 reps × 3 sets
	2	Movement sense training with laser feedback	
		Sitting position	
		- Tracing an intricate pattern at a slow speed (a figure of eight/zig-zag/alphabet)	5 reps × 3 sets
	3	Movement sense training with laser feedback	
		Sitting position	
		- Tracing an intricate pattern at a fast speed (a figure of eight/zig-zag/alphabet)	5 reps × 3 sets
Oculomotor control	1	Eye follow, gaze stability and eye-head coordination	
		Sitting	
		- Eyes following a target with slow speed while keeping the head still (vertical/horizontal)	5 reps × 3 sets
		- Head moving while fixing eyes on a single spot (vertical/horizontal)	5 reps × 3 sets
		- Eyes and head moving together to the same direction (vertical/horizontal)	5 reps × 3 sets
	2	Eye follow, gaze stability and eye-head coordination	
		Sitting	
		- Eyes following a target with fast speed while keeping the head still (vertical/horizontal)	5 reps × 3 sets
		- Head moving while fixing eyes on complex targets (vertical/horizontal)	5 reps × 3 sets
		- Moving the eyes first then the head to the same direction	5 reps × 3 sets
	3	Eye follow, gaze stability and eye-head coordination	
		Sitting	
		- Eyes following a target with neck in 45° torsion (vertical/horizontal)	5 reps × 3 sets
		- Head moving while fixing eyes on a word target with complex backgrounds (vertical/horizontal)	5 reps × 3 sets
		- Eyes and head moving to the opposite direction (vertical/horizontal)	5 reps × 3 sets
Balance control	1	Static balance	
		Standing	
		- Narrow stance (firm/soft surfaces with eyes open/closed)	30 s holds × 10 reps
		- Tandem stance (firm/soft surfaces with eyes open/closed)	30 s holds × 10 reps
	2	Dynamic balance and gait	
		Standing	
		- Throwing/catching a ball while tandem stance (firm/soft surfaces)	30 s holds × 10 reps
		Walking	
		- Normal walking with fast speed (forward/backward, side way)	10 reps
		- Tandem walking (forward/backward)	10 reps
	3	Dynamic balance and gait with head movement	
		Standing	
		- Throwing/catching a ball while single leg standing (firm/soft surfaces)	30 s holds × 10 reps
		Walking	
		- Normal walking (forward/backward, side way) with head movement (left/right, up/down)	10 reps
		- Tandem walking (forward/backward) with head movement (left/right, up/down)	10 reps

### Outcome measures (Table 5)

#### Primary outcomes

##### Postural stability

A sway meter will be used to measure the extent of postural sway and displacement. The sway meter is a simple tool for assessing postural sway in individuals with impaired balance [38]. It has been shown to have good test-retest reliability (ICCs = 0.65-0.94) and good validity (r with forceplate = 0.56-0.87) [38]. The sway meter consists of a 40 cm long rod with a vertically mounted pen at its end. It will be firmly attached to the participant’s waist using a webbing strap. During the test, the pen will record participant’s sway on a millimeter graph paper fastened to the top of an adjustable-height table. Maximum displacement in anterior-posterior (APmax) and medial-lateral (MLmax) directions and total sway (number of square millimeter squares traversed by the pen) will be recorded. The postural sway will be measured in 8 conditions as follows: narrow stance (feet close together) on firm and soft surfaces with eyes open and eyes closed [39] and during a neck torsion maneuver (head turned 45° to the left and right) on firm and soft surfaces [40]. Participants will be tested barefoot and asked to stand still without talking for 30s for each condition. Participants are allowed a maximum of two additional attempts if they are unable to maintain the position for 30s. A rest period of 60s will be given between each condition.

**Table 5 Tab5:** Summary of outcome measures

Primary outcome measures	Data collection instruments
Postural stability	A swaymeter
- Sway displacement	
- Sway area	
Cervical joint position error	A laser-pointer attached to a lightweight headband
Secondary outcome measures	
Gait speed	10-m walk test
Dizziness intensity	VAS (0-100 mm)
Neck pain intensity	VAS (0-100 mm)
Neck disability	NDI-TH (0-100)
Pain extent and location	iPad and custom software
Cervical range of motion	A CROM instrument
Functional ability status	PFSF (scale range 0-10)
Health-related quality of life	Thai SF-36 (scale range 0-100)
Global perceived benefit of treatment	A seven-point ordinal Likert scale (1-7)

All outcome measures will be recorded at baseline, immediately after intervention, 3, 6 and 12 months follow-ups. *VAS* Visual analogue scale, *NDI-TH* Neck disability index-Thai version, *Thai SF-36* Thai version of short form 36, *CROM* Cervical range of motion, *PFSF* The patient-specific functional scale

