**Methods:**

A 2 × 2 factorial, single blind RCT with immediate, short- and long-term follow-ups. One hundred and sixty eight participants with neck pain with impaired joint position sense and balance will be recruited into the trial. Participants will be randomly allocated to one of four intervention groups: i) local neck treatment, ii) local treatment plus tailored sensorimotor exercises, iii) local treatment plus balance exercises, and iv) local treatment plus sensorimotor and balance exercises. Participants receive two treatments for 6 weeks. Primary outcomes are postural sway and cervical joint position error. Secondary outcomes include gait speed, dizziness intensity, neck pain intensity, neck disability, pain extent and location, cervical range of motion, functional ability, perceived benefit, and quality of life. Assessment will be measured at baseline, immediately after treatment and at 3, 6, 12 month-follow ups.

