##### Cervical JPE

Cervical JPE will be measured using a laser-pointer attached to a lightweight headband as described by Revel et al. [13]. Participants will be seated 90 cm away from the target. They will be blindfolded and asked to perform an active movement (extension and rotation to the left and right) and return to the starting head position as accurately as possible. An absolute error between the starting and end points will be calculated in millimeters and then converted to degrees. Three repetitions of each movement direction will be undertaken and the mean value of the error will be used for analysis. This method has been shown to have good test-retest reliability (ICCs = 0.73-0.84) and high validity (r with three-dimensional ultrasound based technique = 0.95) [41].

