### Statistical analysis

SPSS version 17.0 or higher will be used for statistical analysis. Descriptive statistics will be used to describe demographic data and baseline characteristics and follow-ups for each treatment group. Two-way mixed ANOVA will be used to determine within-subject and between subject variables. Main effects for independent variables (local treatment/sensorimotor exercise and local treatment/balance exercise) and the intervention effects of the independent variables immediately after treatment and at 3, 6 and 12 month follow-ups will be analyzed. This allows the individual effects of sensorimotor exercise and balance exercise to be examined as well as whether there will be an additive effect of applying both sensorimotor and balance exercises in a multimodal treatment. Differences in mean change (baseline minus follow-up) will be compared between groups using baseline values of the outcomes as covariates.

Effect sizes will be calculated by taking the difference in mean changes in the primary outcomes between the intervention groups and control group (local neck treatment alone). An effect size of 0.2 will be regarded as small, 0.5 as medium and 0.8 as large [55]. Main comparative analysis for primary and secondary outcomes will be performed using an intention-to-treat approach. To address missing data, multiple imputation will be performed as a sensitivity analysis. The significance level will be set at 0.05.

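### Neither primary outcome is reduced to one variable, visit or contrast, and a flat 0.05 is the only error rule, so the primary claim is not held at 5% if either outcome can carry it

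*Protocol article*

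**What the plan says.** The abstract states: "Primary outcomes are postural sway and cervical joint position error". The Postural stability section sets out what is collected: "Maximum displacement in anterior-posterior (APmax) and medial-lateral (MLmax) directions and total sway (number of square millimeter squares traversed by the pen) will be recorded". It continues: "The postural sway will be measured in 8 conditions as follows". These are a narrow stance on two surfaces with eyes open or closed, and neck torsion to each side on the same two surfaces. Table 5 lists sway displacement and sway area together as primary.

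Under Cervical JPE, participants "perform an active movement (extension and rotation to the left and right") and return to the start. On data reduction the section says "Three repetitions of each movement direction will be undertaken and the mean value of the error will be used for analysis". This can mean one mean per direction or one mean overall.

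Statistical analysis plans a two-way mixed ANOVA with main effects of sensorimotor and balance exercise, and a look at whether the two together add to each other. It says that the "intervention effects of the independent variables immediately after treatment and at 3, 6 and 12 month follow-ups will be analyzed". It also plans baseline-adjusted comparisons of mean change. Its only error rule is "The significance level will be set at 0.05".

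Sample size uses one sway difference (21.9 cm², SD 12.3) and one JPE difference (4.5°, SD 3.2). It names no sway condition, JPE direction or visit.

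**The concern.** A primary outcome fixes in advance which result decides the trial. Here two labels cover up to 27 measured variables, four follow-ups and two or three factorial effects, and nothing ranks them. The primary hypothesis is superiority for neck proprioception and balance, but the article does not say whether one outcome suffices or both are needed, or which exercise has to affect which outcome.

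A superiority claim could therefore rest on whichever metric, stance, direction or visit falls below 0.05. The 5% attached to each test is then not the error rate of the trial's conclusion. The Discussion expects that conclusion to inform practice guidelines.

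**Working it through.** **The plan's own figure.** The article states no familywise error rate. Its 0.05 is the error rate of a single test.

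**Counting, from the article.**
- Sway: 3 measures × 8 conditions = 24 variables.
- JPE: 3 directions, or 1 if averaged. Total 27, or 25.
- Follow-ups: 4 (post-treatment, 3, 6 and 12 months).
- Effects: 2 main effects, or 3 with the combination.
- Widest count: 27 × 4 × 2 = 216 tests, or 27 × 4 × 3 = 324.
- One test per variable and effect, none per visit: 27 × 2 = 54, or 27 × 3 = 81.
- Narrowest count, one sway and one JPE variable with one test per effect: 2 × 2 = 4, or 2 × 3 = 6.

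**Formula.** For m independent two-sided tests with no true effect, P(at least one rejection) = 1 − 0.95^m. Correlated tests were simulated as two-sided z-tests at 0.05 under the global null. Assumptions: equal correlation r among sway variables and among JPE directions, a common correlation between visits, a sway–JPE correlation of at most 0.1, and independent factorial effects. The article gives no correlations.

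**Results when either outcome suffices.**

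| Reading | Assumed correlation | 2 effects | 3 effects |
|---|---|---|---|
| 1 sway + 1 JPE, one test per effect | independent | 1 − 0.95^4 = 0.19 | 1 − 0.95^6 = 0.26 |
| same | sway–JPE 0.1 | 0.18 | 0.27 |
| 1 sway + 1 JPE, 4 visits | independent | 1 − 0.95^16 = 0.56 | 1 − 0.95^24 = 0.71 |
| same | visits 0.7 | 0.42 | 0.57 |
| same | visits 0.6 | 0.46 | 0.60 |
| 27 variables, one test per effect | variables 0.7 | 0.62 | 0.78 |
| 27 variables, 4 visits | variables 0.5, visits 0.7 | 0.98 | 0.997 |
| same | variables 0.7, visits 0.7 | 0.93 | 0.98 |
| same | variables 0.9, visits 0.9 | 0.62 | 0.77 |

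**Counting only results that favour the added exercise.** Each test then has a one-sided level of 0.025. The narrowest reading gives 1 − 0.975^4 = 0.10, or 1 − 0.975^6 = 0.14. One sway and one JPE variable at four visits, two effects, visit correlation 0.6: 0.26. All 216 tests: about 0.36 (correlations 0.9 and 0.9) to about 0.90 (variables 0.3, visits 0.6).

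**Which sway quantity was powered.** 100 mm² = 1 cm², so a difference in cm² matches total sway, counted in millimetre squares, and the sway area of Table 5. The measure can be identified. The stance condition, or average over conditions, and the visit cannot.

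**The case against.** A reader might infer that 216 or 324 tests are planned and that a false-positive primary result is close to certain. The article does not support that. It says the sway measures will be recorded, not that each is a separate primary test. A mixed ANOVA may give one test per effect across visits, and the sample size points to one sway and one JPE quantity. Near-certainty needs the widest count, no effect of either exercise and only moderate correlation. APmax, MLmax and total sway come from the same pen trace, so high correlation is plausible. This stands, and it is why the result is given as a range.

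A reader might also infer that the powered sway quantity matches nothing recorded. The units show otherwise, as set out above.

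The hypothesis can be read as requiring both outcomes. If both must favour the same exercise, the narrowest reading gives about 2 × 0.025² = 0.001, well under 5%. With all 27 variables, r from 0.3 to 0.7 and visit correlation 0.6, it is about 0.10 to 0.21; at 0.9 and 0.9 it falls to about 0.03. So inflation is not universal. It depends on a success rule that the article does not state.

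Finally, multiplicity procedures are often left to an analysis plan, and one may exist. That covers the mechanics of adjustment. It does not cover which measurement and visit make up the primary outcome: the article itself puts displacement and area under primary, schedules four analysis visits and sets 0.05 without ranking them.

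**Conclusion.** The point holds as an insufficiently defined primary endpoint tested at an unadjusted 0.05. With an either-outcome rule and no true effects, the two-sided familywise error exceeds 5% on every reading examined:
- about 0.18 to 0.26 with one test per outcome and effect;
- about 0.42 to 0.46 with one sway and one JPE variable at four visits and two main effects;
- about 0.6 to above 0.99 with all 27 variables at each visit.

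If only results favouring the added exercise count, the narrow readings are roughly halved and the widest becomes about 0.36 to 0.90. The counts come from the article. The correlations, the either-outcome rule and the global null are assumptions. The article does not show which reading will be used, so no single figure should be quoted as the trial's error rate.

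**What to change.** Before unblinding, state in the protocol or analysis plan:

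1. One sway variable: total sway area, in one named condition or averaged over the eight.
2. One JPE variable: mean absolute error over the three directions.
3. One primary visit, chosen by the investigators. The article seeks both short- and long-term benefit, so the choice is theirs.
4. The confirmatory contrasts, tested with Holm at an overall two-sided 5%. Either the two matched main effects (sensorimotor on JPE, balance on sway), or all four main effects. The Background places the cross-effects within the primary objective, so a two-contrast plan should say openly that they become secondary.
5. All other metrics, conditions, directions and visits as secondary, reported with confidence intervals.

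**Cost.** No new data or participants are needed. The first Holm step becomes 0.05/2 = 2.5% for two contrasts or 0.05/4 = 1.25% for four. For a main effect with 70 against 70 (the 35 per group in Sample size), the standardised difference detectable at 80% power is about (z + 0.842) × √(2/70). This gives (1.960 + 0.842) × 0.169 = 0.47 at 5%, (2.241 + 0.842) × 0.169 = 0.52 at 2.5%, and (2.498 + 0.842) × 0.169 = 0.56 at 1.25%. The article's assumed effects, 21.9/12.3 = 1.78 and 4.5/3.2 = 1.41, are far larger. The other cost is that fewer results can be called confirmatory.
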